#### Descriptive analyses at baseline

Baseline comparability between groups will be tested using Pearson’s chi-square test or Fisher’s exact test for categorical data, and Mann-Whitney’s *U*-test for continuous data. All baseline measurements will be analyzed.

#### Primary analysis

Treatment differences will be assessed on the percentage change from baseline to the three follow-up visits. Our primary analysis will be conducted regarding the effect of PEMFs on BMDF at 6 months. Descriptive statistics for this variable will be presented for each intervention group at each appointment during the 6-month follow-up. Comparisons will be carried out using a mixed linear model [34] with treatment group as a fixed factor and time as a random factor. Adjustments will be made for covariates including participant’s age, menopause age, time since menopause, BMI, and the corresponding baseline value. This model is supposed to be able to appropriately control for correlation among multiple observations. Sensitivity analysis will also be carried out by independent t-tests comparing changes between groups from baseline to the end of follow-up. When intragroup comparison is needed, paired sample *t*-tests will be also applied.

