### Assessment

The primary outcome will be the mean percentage change in BMDF at 6-month follow-up. Proposed secondary outcomes were listed below: VAS; The mean percentage changes in bone mineral density of the lumbar spine (BMDL); serum 25-hydroxy-vitamin D (25(OH) D) concentrations; Oswestry Disability Index (ODI); manual muscle test (MMT) score; Berg Balance Scale (BBS) score; Timed Up and Go Test (TUG); hemorheological determinants; serum C-terminal telopeptide of type I collagen (sCTX I), serum bone alkalin phosphatase (sBALP), N-MID osteocalcin (N-MID); range of motion (ROM) of lumbar spine; overall functional ability using short form 36 item general health questionnaire (SF-36, Quality Metric, Inc., Lincoln, Rhode Island, USA); treatment compliance; health care consumption costs; possible adverse events (Additional file 1). Detailed information on some of the outcome measurements are described below:

As for BMD measurements, participants will be scanned in the standard manner by a technician using DXA (GE Lunar iDXA with encore 12.0 software, GE Healthcare Lunar, Madison, WI) following recommendations from the manufacturer. For proximal femur, BMD of the total hip will be recorded and analyzed, while for the lumbar spine the average BMD (aBMD) of the four vertebrae (L1-L4) will be extracted. All these data could be directly obtained using corresponding software without further calculations.

Manual muscle strength of the lumbar and the lower-extremity will be estimated by employing the MMT method with the traditional six-point ordinal Medical Research Council scale (0 to 5). Half-point scores will be used between all grades except that of 4 and 5, since it requires manual resistance that cannot be graded reliably [30]. All tests will be performed by a single examiner. Furthermore, before testing, the examiner and participants will all be required to rest for at least 5 min.

The BBS is a set that comprises 14 simple balance related tasks, ranging from standing up from a sitting position, to standing on one foot [31]. Another examiner will perform the tests for all the participants following the standard procedure. The examiner and participants will also be required to rest for at least 5 min before testing.

A TUG test will be conducted by recording the total time that a person takes to rise from a chair, walk 3 meters, turn around, walk back to the chair, and sit down [32]. It is intended to evaluate the functional mobility of the participants.

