### Follow-up

After the first 5 weeks after enrollment, all participants are scheduled to receive only usual care and the research will go into the follow-up phase with scheduled follow-up visits taking place at 5 weeks, 3 months and 6 months after enrollment (Additional file 1). The last two time points are designed to explore possible delayed effects of PEMFs.

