#### Secondary analyses

The analyses for the secondary outcome measurements will be carried out in the same way as those mentioned above. A mixed linear model will be applied, with treatment group as a fixed factor, and time as a random factor, adjusting for similar confounding factors. In addition, to explore relationships among variables, we will calculate Spearman’s or Pearson’s correlation coefficients along with their *P* values.

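### As worded, the primary mixed model estimates a difference averaged over three visits, not the 6-month effect, and read literally it does not model correlation within a participant

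*Protocol article*

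**What the plan says.** The target is clear. The Assessment section states "The primary outcome will be the mean percentage change in BMDF at 6-month follow-up", and the Primary analysis section agrees: "Our primary analysis will be conducted regarding the effect of PEMFs on BMDF at 6 months".

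The data entering the comparison are wider than that target: "Treatment differences will be assessed on the percentage change from baseline to the three follow-up visits". The model for them is "a mixed linear model [34] with treatment group as a fixed factor and time as a random factor". Covariates follow: "Adjustments will be made for covariates including participant’s age, menopause age, time since menopause, BMI, and the corresponding baseline value". The section then says of the model: "This model is supposed to be able to appropriately control for correlation among multiple observations". No interaction of treatment with time, no participant effect and no within-participant covariance is named.

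The Secondary analyses section repeats the specification: "A mixed linear model will be applied, with treatment group as a fixed factor, and time as a random factor". The Follow-up section explains the later visits: "The last two time points are designed to explore possible delayed effects of PEMFs".

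The Primary analysis section also plans independent t-tests on the change to the end of follow-up, as a sensitivity analysis. The Data analysis section fills missing outcomes by LOCF.

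**The concern.** Two features of the stated model do not fit its stated purpose.

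- **Quantity estimated.** With treatment as the only fixed design factor, there is one treatment coefficient for all visits. That is an average over visits, while the primary outcome is the difference at one visit. If the effect changes over time, the primary estimate and test address a different question from the one declared.
- **Correlation.** The participant is the unit measured repeatedly, but time is the only random factor. A random time effect is shared by everyone seen at the same visit. It correlates different participants within a visit and does nothing to link one participant's three values. The claim that the model handles correlation therefore does not follow from the factors listed. If the model were run that way, the standard error of the treatment difference would be too small.

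Three planned visits are also not a sample from a population of times, so a random time factor is hard to justify in itself. Because the specification is used again for the secondary outcomes, the wording affects more than the primary test.

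**Working it through.** **Inputs from the protocol article.** Three follow-up visits (5 weeks, 3 months, 6 months). 20 evaluable and 25 enrolled per arm. Difference 0.023, SD 0.023, two-sided 5%, power 90%, loss 20%.

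**Assumptions, not in the article.** The within-participant correlation ρ of the three percentage changes after covariate adjustment (0.3 to 0.9); equal variance and equal correlation across visits; the time course of the effect.

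**1. The plan's own figure.** Normal approximation: n = 2 × (1.960 + 1.282)² × (0.023/0.023)² = 21.0 per arm, 22 when rounded up, against the stated 20. Allowing for loss, 20/0.8 = 25, as stated. The gap of two is not the issue here. What matters is that the sample size rests on a two-group comparison at a single time point.

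**2. What the treatment coefficient estimates.** With three rows per participant, the literal model gives (d₁ + d₂ + d₃)/3, where d₁, d₂, d₃ are the differences at the three visits. Relative to a 6-month difference of 1:

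- constant effect: (1 + 1 + 1)/3 = 1.00
- linear growth, with 5 weeks = 35/30.4 = 1.15 months and 1.15/6 = 0.19: (0.19 + 0.50 + 1)/3 = 0.56
- effect only at 6 months: (0 + 0 + 1)/3 = 0.33

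Simulation gave 0.564 and 0.332 for the last two. Adding a participant effect does not change this; only a treatment-by-visit term does.

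**3. Standard error if the model is fitted literally.** With n per arm and residual variance σ²:

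- variance the model uses for the treatment difference: 2σ²/(3n)
- true variance: 2σ²(1 + 2ρ)/(3n)
- true SE divided by model SE: √(1 + 2ρ)
- actual type I error: 2 × [1 − Φ(1.96/√(1 + 2ρ))]

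| ρ (assumed) | SE ratio | Type I error, formula | Simulated, 20 per arm |
|---|---|---|---|
| 0.3 | 1.26 | 12.1% | 13.4% |
| 0.5 | 1.41 | 16.6% | 17.6% |
| 0.7 | 1.55 | 20.6% | 19.9% |
| 0.9 | 1.67 | 24.2% | 23.2% |

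The simulations used 2,000 runs per row, without covariates. n cancels from the ratio, so 25 per arm gives the same formula values. LOCF repeats a participant's own value and so pushes ρ upwards.

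**4. Other readings of the wording** (1,500 runs each, ρ = 0.3, 0.5, 0.7, 0.9).

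- Time as a random slope by participant, no intercept: 10.7%, 12.9%, 17.2%, 24.3%.
- A participant random intercept: 4.5%, 4.8%, 4.2%, 5.3%.

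The second reading restores the nominal level. Neither makes the coefficient a 6-month effect.

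**The case against.** The strongest reply concerns the correlation half. The article never says that there is no participant effect; it names none, and it states the intention to control correlation. The subject identifier and covariance structure are details that a condensed article commonly leaves to the full plan. That stands. A reader might infer that the primary P value is already known to be invalid, but the document does not support this. It supports only that the listed factors, taken literally, do not deliver the property claimed for them.

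A reader might also infer that the design expects an effect that builds up, so that the estimate must be diluted. The Follow-up section speaks only of exploring possible delayed effects. Treatment ends at 5 weeks, so a plateau or a waning effect is equally compatible. With a constant effect of 1 SD, 20 per arm and valid standard errors, the averaged contrast has more power (90 to 96% for ρ = 0.9 to 0.5) than the 6-month test (87%).

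A third tempting step is to add inflated type I error to lost power. With valid standard errors and effects of 0, 0.5 and 1 SD at the three visits, power of the averaged test is about 36 to 47%. The literal model, with its standard errors too small, would reject in about 67 to 70% of such trials. The two harms belong to different models and cannot both be charged to one.

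Finally, the planned t-test does isolate 6 months and needs no within-participant correlation. It is a useful check, but only a sensitivity analysis, so it leaves the primary model uncorrected.

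**Conclusion.** The mismatch of quantity is established from the text. The factor roles are stated in both analysis sections, no treatment-by-visit term is named, and the resulting coefficient is not the 6-month effect unless the effect is constant over visits. The plan leaves room for an effect that is not. The size is unknown: no loss with a constant effect, and 0.56 or 0.33 of the 6-month effect under the two illustrative profiles. A waning effect would push the average above the 6-month value.

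The correlation fault is conditional. If the model is fitted as listed, type I error is roughly 12 to 24% for ρ of 0.3 to 0.9. The direction is certain for any positive correlation; the size rests on assumed values. It falls away if the full plan has a participant effect, and then the first fault alone remains.

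The wording should be settled before the primary analysis is run, since it determines what the primary P value tests.

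**What to change.** In the Primary analysis section, and for the continuous outcomes in the Secondary analyses section:

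- make visit a fixed categorical factor (5 weeks, 3 months, 6 months) and add treatment-by-visit;
- keep baseline BMDF (for a secondary outcome, its own baseline) and the covariates already listed;
- account for repeated measures by participant, with a participant random intercept or a within-participant covariance structure, and say which;
- name the treatment contrast at 6 months as the single primary test;
- fit the model to observed values rather than LOCF-filled rows, and change the LOCF sentence in the Data analysis section to match.

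Restrict the linear model to continuous secondary outcomes; ordinal muscle-test grades, costs and adverse events need methods of their own. If the full plan already contains a participant effect, stating it in one clause settles the correlation half.

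The cost is about a paragraph of text. No new data or participants are needed, and the stated sample size does not change, because it already rests on a comparison at one time point.

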Adverse events will be recorded throughout the study period. Having once occurred, the intensity and possible relationship with the treatment will be examined and described in detail.

Baseline assessment will be carried out after eligibility and informed consent has been confirmed (Fig. 1). Apart from outcome measurements, information referring to participant’s age (in years), menopause age (in years), time since menopause (in years), body mass index (BMI; in kg/m^2^), comorbidities, duration of low back pain symptoms, medication use, information referring to physical activity (evaluated by the International Physical Activity Questionnaire (IPAQ) short version [33]), sunlight exposure (frequency and duration of time spent outside, sun-protective-factor use), employment status, occupation and dietary intake will all be collected.

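### No season or sampling-date term is named for 25(OH)D over a 6-month follow-up; adding one could improve precision, by an amount the protocol cannot fix

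*Protocol article*

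**What the plan says.** The Assessment section lists "serum 25-hydroxy-vitamin D (25(OH) D) concentrations" among the secondary outcomes. Follow-up visits fall at "5 weeks, 3 months and 6 months after enrollment".

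For these outcomes the Secondary analyses section states: "A mixed linear model will be applied, with treatment group as a fixed factor, and time as a random factor, adjusting for similar confounding factors". The factors meant are those of the Primary analysis section, an open list that names age and then "menopause age, time since menopause, BMI, and the corresponding baseline value". That section also sets the scale: "Treatment differences will be assessed on the percentage change from baseline to the three follow-up visits". It allows paired t-tests within a group where such a comparison is wanted.

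Among the baseline data, the Assessment section lists "sunlight exposure (frequency and duration of time spent outside, sun-protective-factor use". Sunlight exposure is not among the named covariates. Season and calendar date are not mentioned anywhere. Under Interventions, all participants receive calcium and alfacalcidol throughout the study.

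**The concern.** The covariate set was written for bone density and is then applied to every secondary outcome. If 25(OH)D follows an annual cycle (an assumption; the protocol does not say so), a woman enrolled near the peak is measured near the trough 6 months later, and the reverse. Women are randomised one at a time as they become eligible, so their enrolment dates differ. The model's time term counts time since enrolment and cannot tell a winter-to-summer change from a summer-to-winter one. Baseline adjustment does not repair this, because at 6 months the seasonal part of the measurement has the opposite sign to that at baseline.

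Two things are at stake for this one outcome: a wider interval for the difference between arms, and paired within-group changes that mix season and usual care with any treatment effect.

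**Working it through.** **Inputs from the protocol.** 20 evaluable women per arm (Sample size section; 20/0.80 = 25 randomised per arm) and a last visit at 6 months. The 20 comes from the BMD calculation; there is no design calculation for 25(OH)D to reproduce. For BMD, 2 × (1.960 + 1.282)² = 21.01, which rounds up to 22, close to the stated 20. Here 20 serves only as the number analysed.

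**Assumed inputs.** Between-person SD 15, within-person SD 8, cosine season with amplitude A (half of peak to trough) of 5, 10 or 15 in the same units, enrolment spread evenly over the year.

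**Step 1: season left out.** Let θ be the enrolment date as an angle. The seasonal part is A·cos θ at baseline and −A·cos θ at 6 months, and cos² θ averages 1/2. Therefore:

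- variance at either visit: V = 15² + 8² + A²/2 = 289 + A²/2
- covariance between visits: C = 15² − A²/2 = 225 − A²/2
- residual variance after baseline adjustment: V − C²/V
- SE of the difference between arms: √(2 × residual variance / 20)

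| A | V | C | Residual variance | SE |
|---|---|---|---|---|
| 5 | 301.5 | 212.5 | 151.7 | 3.9 |
| 10 | 339.0 | 175.0 | 248.7 | 5.0 |
| 15 | 401.5 | 112.5 | 370.0 | 6.1 |

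**Step 2: season in the model.** V = 289 and C = 225, so the residual variance is 289 − 225²/289 = 113.8 and the SE is √(2 × 113.8/20) = 3.4 at every amplitude. Simulation of the fitted model (3000 runs), which pays for estimating the extra coefficients, gives 3.5.

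**Step 3: gain.** From the simulation:

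| A | SE without season | SE with season | Reduction | Equivalent sample size |
|---|---|---|---|---|
| 5 | 3.9 | 3.5 | 11 % | 1.3 times |
| 10 | 5.0 | 3.5 | 30 % | 2.0 times |
| 15 | 6.1 | 3.5 | 42 % | 3.0 times |

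**Step 4: dependence on recruitment spread.** Now express the amplitude in units of the non-seasonal SD of change. For year-round enrolment the variance of the 6-month change is multiplied by 1 + 2A², so season makes up 11 % of that variance at A = 0.25 and 67 % at A = 1.0. With a 3-month recruitment window the share is 0 to 4 % at A = 0.25 and 3 to 42 % at A = 1.0, depending on the months, because a shift common to both arms cancels. With a 3-month window at a seasonal extreme, or an amplitude of about 2 in the units of Steps 1 to 3, the term gains nothing and costs at most about 3 % of the SE.

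**Step 5: validity.** Simulated type I error was 0.045 to 0.056 with or without season terms. The mean estimate was 0.64 to 0.66 for a true difference of 0.65.

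**Step 6: paired within-group test.** Take a 3-month window centred on the peak, A = 5 and no treatment effect. Over ±45° the mean of cos θ is 0.707/0.785 = 0.90, so the mean change is 2 × 5 × 0.90 = 9.0 units in size. The SD of change is about √(2 × 8²) = 11.3, so with 20 women the SE is 11.3/√20 = 2.5 and the ratio is about 3.6. Simulation gave P < 0.05 in 92 % of runs. With enrolment spread evenly over a year the mean seasonal change is zero by symmetry, so this problem needs uneven recruitment.

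**The case against.** The strongest reply is that nothing here is an error. The covariate list is introduced as open, and for secondary outcomes it is only "adjusting for similar confounding factors", so season is unnamed rather than excluded. A covariate for one laboratory marker could sit in a fuller document that is not shown. The protocol does not say that 25(OH)D is seasonal, does not link sunlight exposure to it, and does not state that sampling dates are kept, although scheduled visits make that likely. The calculation uses absolute values at the visit with the largest seasonal contrast, whereas the plan uses percentage change at three visits. Paired tests are optional, and no text says that a within-group 25(OH)D change will be credited to PEMFs.

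All of this stands, and it limits the point to an improvement for one secondary outcome. It does not remove it: the covariates that are named were chosen for bone density, and a calendar term is cheap to name in advance.

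A reader might infer more: that seasonal noise dominates the 25(OH)D comparison, or that it biases it. The documents support neither. Dominance needs an amplitude of about 0.7 or more of the non-seasonal SD of change together with enrolment over much of the year, and neither figure is given. Bias between arms is ruled out on average by concurrent randomisation, although chance imbalance in enrolment season is possible with 20 to 25 per arm. Nor does anything show that the menopause covariates should be dropped for this outcome; that was not tested.

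**Conclusion.** The point holds as a minor one about precision. For 25(OH)D the plan names no season or date term over a follow-up of half a year. Under the assumed SDs and year-round enrolment, the avoidable part of the standard error at 6 months is about 11 % to 42 % for amplitudes 5 to 15. It is close to nil if the amplitude is small or recruitment is short and centred on a seasonal extreme. The protocol does not show which case applies. A paired within-group change in 25(OH)D cannot be attributed to PEMFs, because that test does not separate treatment from season or from the usual care given to everyone. The primary endpoint is not affected.

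**What to change.** For 25(OH)D only, add sine and cosine of the sampling date (or enrolment date) to the pre-specified covariates and keep the existing ones. Baseline sunlight exposure, already collected, is an optional addition. State that paired within-group changes in 25(OH)D are descriptive and are not interpreted as a PEMF effect, because season and the calcium and alfacalcidol given to all participants are not separated from treatment in that test.

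The cost is a line or two of wording, confirmation that sampling dates are recorded, and two degrees of freedom for the sine and cosine pair (one if a summer/winter half-year indicator is used instead). If season turns out not to matter, the loss is at most about 3 % of the standard error. The wording should be fixed before unblinding, so that the term is not chosen afterwards under an open covariate list.

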#### Secondary analyses

The analyses for the secondary outcome measurements will be carried out in the same way as those mentioned above. A mixed linear model will be applied, with treatment group as a fixed factor, and time as a random factor, adjusting for similar confounding factors. In addition, to explore relationships among variables, we will calculate Spearman’s or Pearson’s correlation coefficients along with their *P* values.

#### Health economics evaluation

To determine whether the PEMFs are cost-effective to pay for additional health gain, we will compute mean (and SD) per patient costs and incremental cost-utility ratios using quality-adjusted life-years (QALYs) derived from SF-36 scores with appropriate preference weightings [35, 36].

For all the analyses mentioned above, a two-sided value of *P* <0.05 will be considered statistically significant. All statistical analyses will be carried out using 19.0 SPSS software (SPSS, Chicago, IL).

## Discussion

This paper describes the rationale and protocol for conducting a preliminary RCT in southwest China that will investigate the effectiveness of PEMFs in treating PMO and concomitant lumbar OA.

The idea originated from daily clinical practice since the coexistence of OP and OA is not rare, especially that of PMO and lumbar OA, which is frequently found during BMD examinations using DXA. Furthermore, it was found that excessive bone resorption also took place in the early stage in the development of OA, indicating OP and OA might share the same pathogenic mechanism and could be treated simultaneously [9–12]. As for treatment method, PEMFs have been reported to have anti-osteoporosis and anti-osteoarthritis properties, but whether these two effects would take place at the same time has not yet been evaluated. Since the two skeletal disorders, PMO and lumbar OA, are prevalent among postmenopausal women and have a considerable impact on both individuals and the society [37, 38], it would be of great significance to identify effective treatments that could deal with the two clinical problems simultaneously.

This trial will be the first RCT to investigate the effect and cost-utility of PEMFs for PMO and concomitant lumbar OA. The combination of clinical efficacy and cost-effectiveness evidence is essential for health care decisions. To find improvements for both OP and lumbar OA and to facilitate comparability with other research, we will include valid outcome measurements, and to minimize bias, we will use BMDF, not BMDL, for the diagnosis of OP, eliminating the interference of lumbar OA for measuring BMD. Furthermore, we will choose BMD (specifically the mean percentage change in BMDF), instead of the incidence of fractures, as our primary endpoint, because a change in BMD offers the advantages of high precision, the ability to study multiple skeletal sites in the same patient, and a relatively rapid response to treatment [39, 40]. However, patient relevance of any positive result of this trial will require a follow-up trial with patient-relevant endpoints like fracture and health economics evaluations using QALYs and SF-36 scores informed by fracture data, *etcetera*, to provide further evidence.

We acknowledge limitations in the trial. First, the sample size calculation is somewhat imprecise, and there are many secondary outcomes, all at 0.05 significance in a trial with 25 subjects in each arm after accounting for a 20 % withdrawal. The risk of type I error may be very high. Second, the primary endpoint is BMDF, which is not as patient-relevant as fractures, so relevance of any positive result of this trial to patients needs further investigations in large well-designed trials. In spite of these limitations, our research also has strengths. One is that we refined our exclusion criteria to eliminate potential confounding factors as far as possible. We will exclude patients with confounding disorders and concomitant disorders that are of possibility to interfere with the balance of bone metabolism, and patients with lesions that may not be able to fulfill the study assessment. Furthermore, those who received treatments within 6 months before inclusion will also be excluded. Another one is the utilization of a patient-blinded design, with sham PEMFs arm to reduce the risk of bias. It is of great significance especially for the assessment of patient-reported outcomes (for example, pain), since without a proper patient-blinded design, identified differences could be interpreted as the results of placebo effect, which is found effective in the treatment of OA, especially for pain, stiffness and self-reported function [41]. There are other trials that have used sham PEMFs successfully. For example, Shi *et al*. evaluated outcomes of postoperative delayed union of long-bone fractures treated with an early application of PEMF, as compared with a sham-treated control group, where the coil was applied for 8 h/day with a sham signal generator from the same manufacturer [42]; Nelson *et al*. examined the pain-relieving effect of PEMFs and the sham devices they used were activated with a switch and had blinking indicator lights, just as active devices [43]. These two trials had used sham PEMFs successfully, and their findings were convincing.

In summary, this trial will provide preliminary evidence regarding the use of a nonpharmaceutical, noninvasive modality for managing PMO and lumbar OA. The success of this study will provide scientific evidence to primary care of postmenopausal women with these two common skeletal disorders.

